**Figure 2 F2:**
[figure not shown]
**Flow-chart of randomisation procedure**.

### Blinding

In this trial blinding of the patients is not possible as they either do or do not receive the material belonging to the interventions, and are therefore automatically aware of the intervention group. Since the physicians will not be directly involved in the inclusion of patients they are unaware of the intervention group a patients belongs to. For the assessment of the outcomes during a telephone interview two weeks after discharge the interviewer will be aware of the intervention group a patient belongs to because specific additional questions for each intervention group will be asked to evaluate the interventions. However, the interviewer will not be informed about the background, research questions and outcome measures of this study. For the telephone interview six months after discharge the interviewer will be unaware of the intervention group that the patient belongs to. Finally, the reviewers in the retrospective record review study will be blinded, they will assess some of the outcome measures and should therefore be unaware of the interventions that a patient might or might not have received to prevent possible biases in their assessment.

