##### Evaluation

The use of the leaflet will be evaluated by asking the patient about the added value and the usability of the bundles during a short interview by telephone two weeks after discharge. We will consider the leaflet useful if 60% of the patients says they have used the leaflet and found it useful. The effect of the bundles will be evaluated during the telephone interview two weeks after discharge and by measuring avoidable harm (e.g. adverse medication events, urinary tract infections, wound infections, delirium, falls and pressure ulcers) within 6 months after discharge. The patient will be called again around 6 months after discharge to ask about any medical problems occurring after discharge and their recovery in the past six months. Also, the patient records of all included patients will be reviewed by experienced reviewers for additional information about possible complications and avoidable harm after discharge.

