### General data collection and follow up

After receiving informed consent a questionnaire will be filled out with patient characteristics and the pre-fracture status of the patient. Information about the status before the fracture will be gathered using the 10-item modified Barthel Index for ADL-functioning [42], the Parker and Palmer pre-fracture mobility score [43], the Short Nutritional Assessment Questionnaire [44] and the Delirium Observation Screening Scale [45]. In addition, information will be gathered about the home situation before admission. Before discharge, the questionnaire will be completed with information about the occurrence of pressure wounds, delirium, urinary tract infections, wound infections, falls during admission and possible risk factors after discharge for these complications.

All included patients will be followed for a period of six months after discharge. During this period two interviews by telephone will be held with all included patients, two weeks and six months after discharge. During these interviews patients will be asked some multiple choice questions about their current residence, physical functioning, use of health care, the occurrence of unexpected events and some open end questions about their experiences during the whole care process. In addition to these interviews, the retrospective patient record review study will be conducted to review the patient record up to six months after discharge. The methods of this record review study will be identical to the baseline measurement described earlier. Again, the reviewers will look for complications, adverse events, the quality of record keeping and written information for the transfers of the patient between the different hospital wards. This second record review study will be used to assess the effect of the complete intervention programme on the possible reduction in complications and adverse events.

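### The two-week telephone interviewer knows the group when assessing outcomes, although only the group-specific questions call for it

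*Protocol article*

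**What the plan says.** All places are in the protocol article.

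- **Blinding**, on the two-week call: "For the assessment of the outcomes during a telephone interview two weeks after discharge the interviewer will be aware of the intervention group" to which the patient belongs. The same sentence gives the reason: "the interviewer will be aware of the intervention group a patient belongs to because specific additional questions for each intervention group will be asked". A safeguard follows: "However, the interviewer will not be informed about the background, research questions and outcome measures of this study".
- **Blinding**, on the other assessors: "For the telephone interview six months after discharge the interviewer will be unaware of the intervention group that the patient belongs to", and "the reviewers in the retrospective record review study will be blinded".
- **Study design** and **General data collection and follow up**: both calls, at two weeks and at six months, ask about recovery and include "multiple choice questions about their current residence, physical functioning, use of health care, the occurrence of unexpected events", plus some open questions on experiences.
- **Intervention C, Evaluation**: "The effect of the bundles will be evaluated during the telephone interview two weeks after discharge". The sentence goes on to add avoidable harm measured up to six months, and the section then names the six-month call and the record review as further sources.
- **Intervention B, Evaluation**: the two-week call is where the use and effectiveness of the patient safety card are to be established. The record review is added for complications and adverse events.

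**The concern.** The interviewer needs to know the group in order to ask a recipient about the card or the leaflet. Nobody needs to know it to ask how the patient is walking, whether a doctor was consulted or whether something unexpected happened. As written, the awareness covers outcome assessment in the call as a whole, so a person who knows the allocation records both kinds of answer.

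At stake are the two-week comparisons that bear on research questions 2b and 2c. These rest on patient-level randomisation within the intervention wards, which is the strongest part of the design. If an interviewer prompts, clarifies or records answers differently according to group, the difference enters directly into those comparisons, and randomisation gives no protection against it.

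**Working it through.** No figure in the plan bears on this point. The sample size does not depend on who is blinded, and the article gives no expected frequency for any two-week item. The check is a reading of the sections side by side.

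1. **Is the awareness confined to the extra questions?** No. Blinding attaches it to the assessment of outcomes at two weeks. The justification attaches only to the extra group-specific questions, so the exposure is wider than its stated reason.

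2. **Does the call collect anything besides views on the materials?** Yes. Study design adds recovery. General data collection and follow up adds residence, physical functioning, use of health care and unexpected events. These are asked of every included patient.

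3. **Is the call used to judge effects?** Yes. It is one named source for the leaflet's effect (Intervention C, Evaluation) and for the card's effectiveness (Intervention B, Evaluation).

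4. **Which comparisons are touched?** From Study design and Power calculation, with 80 patients planned per group:
   - Card: groups 2 and 4 against groups 1 and 3, that is 2 × 80 = 160 against 160.
   - Leaflet: groups 3 and 4 against groups 1 and 2, again 160 against 160.

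5. **How does the plan treat its other assessors?**

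| Data | Source | Assessor aware of group? |
|---|---|---|
| Complications and adverse events | Record review | No |
| Six-month patient reports | Six-month call | No |
| Mortality within six months | Objective event | Little room for assessor bias |
| Use and usefulness of card or leaflet | Two-week call, recipients only | Yes, unavoidably |
| Recovery, functioning, health care use, unexpected events at two weeks | Two-week call, all patients | Yes, avoidably |

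Blinding says that the record reviewers should not know the interventions because they assess outcomes. The same argument applies to the last row, which is the exception.

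6. **Is the gap closed elsewhere?** No section separates the common items from the group-specific ones. Strengths and limitations of the study names unblinded patients and the researchers' presence on the wards as possible sources of bias, but not the unblinded two-week interviewer.

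7. **Do the blinded sources fully replace the call?** Not entirely. Strengths and limitations of the study concedes that record review finds post-discharge adverse events only if they lead to readmission or reach the outpatient record. Milder early problems depend on what patients report in the calls.

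**The case against.** The case against is substantial.

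- **The primary outcomes are largely protected.** Complications and adverse events are judged by blinded reviewers, mortality is objective, and mobility at six months falls at the time of the blinded call. A reader might infer that the trial's main results are compromised. The article does not support that. The two-week common items are not even listed under Outcome measures.
- **The only thresholds fixed for this call are 60% use-and-usefulness criteria among recipients.** These involve no between-group contrast. That is correct, but the Evaluation sections also assign the call a role in judging effect, which goes beyond the thresholds.
- **The common items are multiple-choice.** Closed questions leave less room for prompting and coding. They leave some, since an interviewer still explains options and resolves unclear answers by telephone.
- **The interviewer is kept naive.** This is a real safeguard. It is incomplete, because someone who asks only certain patients whether a leaflet helped can guess what is being tested.
- **The order of questions is not given.** A reader might infer that the group is known from the first moment of the call. The article states neither when it is disclosed nor how the form is laid out, so that reading is not supported. What the text does say is that the interviewer is aware for the assessment of outcomes.
- **Patients are unblinded in any case.** Their own reporting bias would survive any change to the call. This limits what the fix achieves, but it does not justify adding an interviewer component.

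**Conclusion.** The point holds in a limited form. The plan lets an interviewer who knows the group collect common, patient-reported items at two weeks, for a reason that applies only to other questions. The between-group comparisons of those items, and the two-week part of the leaflet and card evaluations, are open to interviewer bias that the trial could avoid at almost no cost.

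The size is unknown. The article gives neither the frequency of the two-week items nor any basis for the amount of differential recording, so an inflated error rate could be calculated only from arbitrary inputs, and none is offered here.

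Two assumptions are made. The first is that the two-week common items will be compared between groups, as the Evaluation sections imply. The second is that six-month mobility is obtained in the blinded six-month call, which fits its timing although the article does not name the source.

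**What to change.** Split the two-week call form into two parts.

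1. Ask and record the common items first, in identical form for every patient including controls, with the randomised group not disclosed to the interviewer.
2. Then open the group-specific module for that study number and ask about use and usefulness.

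State in Blinding and in the Evaluation sections for Interventions B and C that only the first part is used for between-group comparisons at two weeks. The second part then serves to describe recipients' experience and to check the 60% criteria.

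Add the remaining bias to Strengths and limitations of the study: patients are unblinded and may reveal their group during the first part, and the control hospital may be recognisable to the interviewer.

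The cost is a slightly more complex form. No extra staff, calls or patients are needed.

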### Baseline measurement (Research question 1)

#### Aim

The aim of the baseline measurement is to determine the nature and scale of unintended events in elderly patients with a hip fracture. In addition, the reviewers will also evaluate the quality of the record keeping and the completeness of the transfer of information in the patient record. This information will be used as a starting point to evaluate the effects of the intervention study.

#### Background

Retrospective patient record review is a method that has been used to study AEs in hospitals in several countries [10,13,38]. The methods and review form used in this study will be based on the Dutch Adverse Event Study [34,39]. They used a method that was based on a protocol originally developed by the Harvard Medical Practice Study, which studied the incidence of AEs in New York State hospitals in 1984 [38].

#### Method

The incidence of complications and AEs will be measured within the care chain and especially during the hospital admission of elderly hip fracture patients. In this study we look at the care chain from the moment that the patient is brought into the emergency department until six months after discharge from the hospital. Therefore the patients' hospital record will be studied in retrospect by an experienced surgeon. For the baseline measurement patient records of hip fracture patients acutely admitted in 2007, the year previous to the start of the intervention study, will be reviewed using a structured review form. In each hospital all surgical and orthopaedic admissions of patients with a hip fracture of 65 years or older will be selected. Of these selected index admissions the medical, nursing and, if existing, the outpatient records will be collected, the X-rays made during the admission will also be available. Records of patients with a pathological fracture, polytrauma or elective admission will be excluded. The main outcome variables in this part of the study are: rate of complications, adverse events, near misses and information transfer between care providers.

The patient records will be reviewed by a team of eight experienced reviewers. The selection criteria for the reviewers are:

• At least ten years post graduate clinical (surgical) experience;

• Surgical experience with hip fractures;

• Good reputation among colleagues;

• No longer than 8 years retired at the start of the study;

• Experience or affinity with analysis of incidents, complaints and errors.

Most of the reviewers have participated in a previous record review study [39] and therefore are already familiar with this type of research, terminology and methodology. Nevertheless, they will all follow a half-day training led by the research team and one experienced reviewer. During this training, the definitions, study protocol, adjusted review form and examples of AEs will be discussed. The reviewers will also receive a review manual. They will be compensated for their review activities at an hourly rate for expenses. During the review process the reviewers can ask advice from a general internist about accepted clinical practice in the specialty of internal medicine.

The records will be reviewed by one reviewer and he determines whether complications, an adverse event or a near miss have occurred during the index admission to the hospital or the six months following the index admission using a paper based structured review form. This review form will be adapted from the Dutch Adverse Event Study [34,39] and adjusted and specified for this patient group. The review form starts with general characteristics of the admission and possible complications. Next, if the surgeon determines that an adverse event is present, the review will be continued with questions about the nature and impact, location and involved specialty, classification, preventability and causes of the adverse event. The last part of the review form will be about the clarity and completeness of information in the patient record for the transfers of the patient between the different wards and specialties within the hospital.

A random sample of 10% of the records will be independently reviewed by a second reviewer to assess the variation in the review process between reviewers.

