### Aim and research questions

The aim of this randomised controlled trial (RCT) is to evaluate the effectiveness of a patient safety intervention programme for elderly hip fracture patients. Therefore, the following research questions will be addressed:

1. What is the nature and scale of adverse events and avoidable harm in the care chain for elderly hip fracture patients?

2. How is it, in the total care chain of elderly hip fracture patients, possible to reduce risks and unintended harm, and to ensure that complex care processes proceed more safely? This research question is divided into sub-questions for the three interventions:

a What is the effectiveness of the SBAR communication tool on unintended events and avoidable harm during hospital stay? (Intervention A)

b What is the effectiveness of a patient safety card with guidelines for patients and their families on signalling errors and patient trust in health care? (Intervention B)

c What is the effectiveness of evidence based bundles with regard to unintended events in the period after discharge? (Intervention C)

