### Participants

The following inclusion criteria will be used to select eligible patients for participation in the study:

• The patient is acutely admitted to the surgical ward with a hip fracture during the research period;

• The patient is not admitted with polytrauma;

• The hip fracture is not a pathological fracture;

• The patient is 65 years of age or older;

• The patient will be operated on the hip fracture;

• The patient does not participate in an interfering study;

• The patient is in a good cognitive condition to fully understand the information about the study and to give Informed Consent.

Patients will be recruited as quickly as possible after admission to the hospital. The patients will be included by the nurses working in de wards, this process will be closely monitored by the researchers. When a patient is eligible for participation the study will be explained to them and Informed Consent will be asked. If the inclusion by the nurses does not work out as intended, the researchers will have to take over this part of the data collection.

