### Outcome measures

The primary outcome measures in this study are the incidence of complications and adverse events, mortality rate within six months after discharge and functional mobility six months after discharge. Secondary outcome measures are length of hospital stay, quality and completeness of information transfer and patient satisfaction with the instruments.

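### The record-review window starts at emergency department arrival, so the card contrast, and any leaflet contrast on the pooled complication and adverse-event outcome, counts events that the randomised material could not affect

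*Protocol article*

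**What the plan says.** The window is set in the Method text of the baseline measurement (research question 1): "we look at the care chain from the moment that the patient is brought into the emergency department until six months after discharge from the" […]. Later in the same section the reviewer judges whether events "have occurred during the index admission to the hospital or the six months following the index admission". This wording names the admission rather than the emergency department as the start, and does not say whether the six months run from admission or from discharge.

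General data collection and follow up carries the method into the trial: "The methods of this record review study will be identical to the baseline measurement described earlier". It also states the purpose: "This second record review study will be used to assess the effect of the complete intervention programme on the possible reduction in complications and adverse" […].

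Under Outcome measures, "The primary outcome measures in this study are the incidence of complications and adverse events, mortality rate within six months after discharge" and mobility at six months. Mortality and mobility are tied to the period after discharge. The complication and adverse-event outcome has no start point of its own, and no text excludes events before inclusion.

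The randomised material comes later than the start of the window. Under Participants, "Patients will be recruited as quickly as possible after admission to the hospital". Under Intervention B the card is handed over during the stay. The leaflet's research question concerns the time after discharge: "What is the effectiveness of evidence based bundles with regard to unintended events in the period after discharge? (Intervention C"). SBAR is not randomised; it applies to everyone on the intervention wards (Randomisation).

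**The concern.** A window from the emergency department onwards suits research question 1, which describes the whole care chain. It suits a randomised comparison of the card or the leaflet less well. A patient who has a complication before inclusion is an any-event case whichever envelope is opened. For a leaflet comparison on the pooled outcome, the same is true of every in-hospital event. Several of the leaflet's targets (delirium, urinary tract and wound infection, falls, pressure ulcers) are also recorded as events during admission, so some patients would already be cases before the leaflet's target period begins.

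At stake is the power to see an effect of the card or the leaflet on a primary outcome. A useful material could look weaker than it is, because part of the outcome was settled before it could work.

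**Working it through.** **Inputs from Power calculation:** absolute reduction 5 points, SD 10%, alpha 0.05 (two-sided reproduces the figure), power 80%, 64 per group, 80 with drop-out.

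**Input not in the protocol:** q, the share of patients with an event before the material can act. The Background section states that no adverse-event rate has been published for this patient group. A range is therefore shown as an assumption.

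**Step 1: reproduce the plan's figure.** n = 2(1.960 + 0.842)² × (0.10/0.05)² = 2 × 7.849 × 4 = 62.8, so 63 per group. The t-test version gives 63.77, so 64, as stated. Drop-out: 64/(1 − 0.20) = 80. Power at 64 = Φ(0.05/(0.10 × √(2/64)) − 1.960) = Φ(0.868) = 81%.

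**Step 2: dilution.** Let p₁ and p₀ be the risks of an event after the material can act, independent of earlier events. The any-event risk over the full window is q + (1 − q)p. The difference is (1 − q)(p₁ − p₀).

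**Step 3: put the diluted difference into the plan's own formula** (normal approximation, SD 10%).

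| q (assumed) | Difference, points | n per group for 80% | Power at 64 |
|---|---|---|---|
| 0 | 5.0 | 63 | 81% |
| 0.10 | 4.5 | 78 | 72% |
| 0.20 | 4.0 | 99 | 62% |
| 0.30 | 3.5 | 129 | 51% |
| 0.50 | 2.5 | 252 | 29% |

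The required size grows by 1/(1 − q)²: 1.23 at q = 0.10, 1.56 at 0.20, 2.04 at 0.30.

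**Step 4: how far this depends on the set-up.**
- *Pooled groups.* If the card contrast combines groups 2 and 4 against 1 and 3, there are 2 × 64 = 128 per side. Power is Φ(0.05(1 − q)/(0.10 × √(2/128)) − 1.960) = Φ(4.0(1 − q) − 1.960), or 98%, 95%, 89% and 80% at q = 0, 0.10, 0.20 and 0.30. The shrinkage of the estimate is the same.
- *Yes/no variance.* An SD of 10% does not fit a yes/no outcome: at a 20% risk it is √(0.20 × 0.80) = 40%. Taking later risks of 20% v 15% (assumed), the usual two-proportion formula needs 906 per arm at q = 0, 1481 at 0.10 and 2201 at 0.20. The SD is a separate and larger problem than the window.
- *Mean number of events.* Data analysis also uses the mean count. Early events add equally to both means, so the absolute difference is kept and only the variance rises. With assumed Poisson means of 0.50 v 0.45, n per arm is (0.95 × 7.849)/0.05² = 2983. With 0.1 early events per patient added to each mean it is (1.15 × 7.849)/0.05² = 3611.

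**The case against.** The strongest case on the other side has five parts.

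- **The wide window has a purpose.** The second record review is meant to assess the whole programme, and the baseline serves as the reference for it. That comparison needs the same window on both sides, and 2007 records have no inclusion date. This stands: the full window must stay for the programme comparisons.
- **The leaflet has its own window.** The Evaluation text of Intervention C measures avoidable harm within six months after discharge and uses the record review for complications after discharge. This stands. A reader might infer that every randomised contrast is diluted, or that the leaflet is judged only on a count that includes the hospital stay. The protocol does not support either. Mortality and mobility are also post-discharge outcomes, and SBAR has no patient-level randomised contrast to dilute. What remains for the leaflet is that Outcome measures does not adopt this post-discharge window for the primary complication and adverse-event outcome, so a contrast on the pooled outcome would be diluted.
- **The card's early share may be small.** Recruitment is meant to be fast, the limitations text says that patients get the material straight after inclusion, and the definition of a complication requires medical treatment to have begun. This is plausible. The size for the card is unknown and may be modest.
- **The 5 points belong to the whole programme.** The protocol states no effect for the card or the leaflet alone. This stands. The table shows what dilution does to a difference of that size; it does not claim that either material was expected to achieve it.
- **Early events are balanced by randomisation.** This is correct. A reader might fear a false positive finding; there is no mechanism for one here.

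**Conclusion.** The point holds for the card v no-card contrast, and for any leaflet v no-leaflet contrast on the pooled complication and adverse-event outcome, when the measure is any-event incidence. There the difference shrinks by (1 − q). With the protocol's 5 points, SD 10% and 64 per group, power goes from about 81% to 72%, 62% and 51% for q of 0.10, 0.20 and 0.30.

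This rests on an assumed q, on later risk being independent of earlier events, and on the protocol's own SD. The actual loss cannot be found from the protocol. The direction is certain: less power and an estimate nearer to no effect.

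The matter is worth correcting because the remedy is cheap. It does not invalidate the trial.

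**What to change.** 1. Keep the window from emergency department arrival to six months after discharge for research question 1 and for the programme comparisons with the 2007 baseline and the control ward, including SBAR. Starting SBAR's count at inclusion would drop ward events that it could affect.
2. Add an onset date for each complication and adverse event to the review form, which is being adapted anyway. Record the dates of inclusion and discharge.
3. For the card contrast, count events from inclusion to six months after discharge. Inclusion is the right start because patients without a card have no hand-over date.
4. For the leaflet contrast, apply the post-discharge window of Intervention C's Evaluation text to the complication and adverse-event outcome, in patients discharged alive.
5. Report events before inclusion as a baseline characteristic.
6. Align the two statements of the window in the baseline Method section, at both its start and its end.

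The cost is a few date fields and revised outcome wording, with no extra patients. The downside is that some onset dates will be approximate and fewer events will count. The questionnaire completed before discharge already records several in-hospital complications, which helps to separate them from later ones.
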